## Abstract

**Background:**

Bipolar disorder (BD) and borderline personality disorder (BPD) both are severe and chronic psychiatric disorders. Both disorders have overlapping symptoms, and current research shows that the presence of a BPD has an adverse effect on the course of BD. The limited research available shows an unfavorable illness course, a worse prognosis and response to medication, longer treatment duration, more frequent psychiatric admissions, higher drop-out, increased risk of substance abuse, increased risk of suicide, and more impairment of social and occupational functioning. However, there is no research available on the effect of specific psychotherapeutic treatment for this patients.

**Methods/Design:**

This paper presents the protocol of a RCT to investigate the presence of borderline personality features in patients treated for BD (study part 1) and the effectiveness of STEPPS (Systems Training for Emotional Predictability and Problem Solving) added to treatment as usual (TAU) for BD compared to TAU in patients with BD and comorbid borderline personality features (study part 2). STEPPS is a validated and effective intervention for BPD. The study population consists of patients treated for BD at specialized outpatient clinics for BD in the Netherlands. At first the prevalence of comorbid borderline personality features in outpatients with BD is investigated. Inclusion criteria for study part 2 is defined as having three or more of the DSM-IV-TR diagnostic criteria of BPD, including impulsivity and anger bursts. Primary outcomes will be the frequency and severity of manic and depressive recurrences as well as severity, course and burden of borderline personality features. Secondary outcomes will be quality of life, utilizing mental healthcare and psychopathologic symptoms not primarily related to BD or BPD. Assessment will be at baseline, at the end of the intervention, and at 12 and 18 months follow-up.

**Discussion:**

This will be the first randomized controlled trial of a specific intervention in patients with BD and comorbid BPD or borderline personality features. There are no recommendations in the guideline of treatment of bipolar disorders for patients with this complex comorbidity. We expect that a combined treatment aimed at mood disorder and emotion regulation will improve treatment outcomes for these patients.

## Background

Bipolar disorder (BD) is a complex and heterogeneous mood disorder defined by the occurrence of depressive, manic, hypomanic, and mixed episodes, divided by intervals of longer or shorter duration. DSM-IV-TR
[1] classification distinguishes bipolar I disorder (BD-I), bipolar II disorder (BD-II), bipolar disorder Not Otherwise Specified (BD-NOS), and cyclothymia. A study of the World Health Organization
[2] reported that BD is associated with significant functional impairment. There are considerable differences in the acute and prophylactic treatment response among patients with BD. Longitudinal studies show that despite treatment there are often recurrent episodes, residual symptoms, cognitive and psychosocial impairments and functional limitations
[3]. Many questions regarding the course and outcome of BD and factors that lead to an unfavorable outcome are still open to research. There is evidence that the presence of comorbid personality disorder (PD) has an unfavorable impact on the course of BD
[4]. Patients with BD and comorbid PD are more likely to be hospitalized, need more time to achieve symptomatic remission, have more chronic impairments in occupational and social functioning, are less compliant to medication, have greater levels of suicidality, and utilize more psychiatric services than patients with BD without PD
[5]. A review reported that BD patients have a significantly higher prevalence of PD than the general population
[6]. The prevalence of PD in patients with bipolar disorder is estimated between 30% and 40%
[7-10]. This concerns particularly personality disorders from the B and C clusters and in particular borderline personality disorder (BPD). There are considerable areas of clinical overlap between BD and BPD, especially mood instability
[11]. In a sample of 375 patients with a bipolar I or II disorder prevalence of BPD was estimated at 37.3% as screened by PDQ-4+, specified as 34,3% in 169 patients who were euthymic at the time of completing the PDQ-4+, 36,8% in 163 depressed patients, and 51.2% in 43 patients with current (hypo-) mania (personal communication [name]: unpublished data from the Stanley Foundation Bipolar Network). Patients who meet diagnostic criteria for both disorders (BD and BPD) have more frequently a history of substance abuse
[12]. Furthermore there is evidence that the presence of comorbid PD has a negative impact on the course of BD, leading to more mixed episodes and depressive symptoms, a higher suicide risk, a worse therapeutic response, and less treatment adherence
[13]. Given the overlap in clinical presentation of BD and BPD, it has been suggested that there are shared underlying pathophysiological mechanisms
[14],
[15]. Only three publications report the effectiveness of treatment of BD with comorbid BPD. In a matched case–control study Swartz et al.
[16] compared patients who met diagnostic criteria for both BD and BPD with patients with BD without BPD. Both groups received pharmacotherapy and psychotherapy. The results suggest that treatment course may be longer in patients suffering from both BD and BPD. Preston et al.
[12] observed that dimensions of BPD improved significantly with lamotrigine treatment. There was a trend for comorbid bipolar patients to require a second psychoactive medication in addition to lamotrigine during extended treatment. Frankenburg and Zanarini
[17] compared in a placebo-controlled double-blind study the efficacy of divalproex sodium in the treatment of women with BPD and comorbid BD-II. They found that treatment with divalproex sodium significantly decreased irritability and anger, tempestuousness in relationships, and impulsive aggressiveness.

Currently little research exists on the effects of psychological treatments in patients with BD and comorbid borderline personality features or BPD. There are no specific recommendations included in the guidelines for the treatment of BD in this population (e.g., the Dutch guideline
[18]). There clearly is a need to develop new psychotherapies or evaluate existing psychological interventions to improve the course of BD and quality of life as well as reducing mental health care utilization in these patients. This study evaluates the addition of STEPPS (Systems Training for Emotional Predictability and Problem Solving) to treatment as usual (TAU) in patients with BD and comorbid BPD or borderline personality features as described in the inclusion criteria. STEPPS is a cognitive behavioral skills group treatment for BPD developed to improve their emotion regulation. The training consists of 20 weekly sessions of approximately 2,5 hours and has 4 parts: psycho-education, emotion regulation skills, behavioral skills, and emotion handling plan. Two trainers deliver the training. The group size is 8–12 patients. An uncontrolled pilot study presented an indication of the effectiveness of the STEPPS in BPD
[19]. A randomized trial
[20] showed that BPD patients treated with STEPPS compared with TAU showed larger reduction of BPD symptoms, more quality of life and less general psychological symptoms. All improvements were still significant after 6 months. In another randomized trial
[21] STEPPS plus TAU also led to greater improvements in impulsivity, negative affectivity, mood, and global functioning. STEPPS is included in the Dutch guidelines for treatment in BPD
[22]. The underlying assumption is that BPD is characterized by a defect in the individual’s internal ability to regulate emotional intensity. The aim of the training is to gain skills to manage emotions and behavior related problems. Friends and family members provide the “reinforcement team” and learn to reinforce and support newly learned skills of the patients (http://www.steppsforbpd.com).

BPD can be conceptualized as a dimensional or spectrum disorder. Patients may suffer from significant symptoms of BPD without meeting the full diagnostic criteria defined by DSM-IV-TR. To increase the clinical relevance of the present study, both patients with BPD as well as those with borderline personality features are included. For this study patients with borderline personality features are included if they have three or more of the DSM-IV-TR diagnostic criteria, with the additional requirement that these include both impulsivity and anger bursts, since STEPPS training is specifically aimed at improving skills to regulate these symptoms.

The study described in this article will investigate the presence of borderline personality features in patients treated for BD (study part 1). Furthermore it will be investigated in a randomised controlled trial if a specific treatment (STEPPS combined with TAU) compared to TAU only will lead to better clinical outcomes as well as an increased quality of life and less care consumptions (study part 2).

## Methods

### Design

#### Study part 1

Screening for personality disorder with a questionnaire (PDQ4+) in patients with BD treated in a specialized outpatient facility, followed by a semi-structured diagnostic interview (SCID-II) in those patients who screened positive on BPD or borderline personality features relevant for this study. Figure 
1 shows the flow chart of study 1.

**Figure 1 F1:**
[figure not shown]
**Flow chart study 1.** BD = bipolar disorder, BPD = borderline personality disorder, BPF = borderline personality features, NOS = not otherwise specified.

#### Study part 2

A multicenter randomized controlled trial in outpatients with BD and comorbid BPD or borderline personality features. The trial will be carried out in specialized outpatient clinics for BD of large mental health institution in the Netherlands. The inclusion period including all follow-up measurements will be one and a half year. The duration of the intervention phase is 20 weeks. Patients will be recruited through treating psychologist, nurses and psychiatrist. Figure 
2 shows the participant flow of the RCT.

**Figure 2 F2:**
[figure not shown]
**Flow chart study 2.** BD = bipolar disorder, BPF = borderline personality features, TAU = treatment as usual, STEPPS = Systems Training for Emotional Predictability and Problem Solving.

### Participants

Participants of study part 1 are BD patients aged 18–65 years who are currently receiving treatment in specialized outpatient clinics for BD of large mental health institution in the Netherlands. All participants from study part 1 meet the DSM-IV-TR diagnosis criteria of BD-I, BD-II or BD-NOS, verified by Mini-International Neuropsychiatric Interview – Plus
[23]. Respondents who fulfill the criteria for BPD or borderline personality features according to the definition of this study are invited to participate in study part 2. They are approached by letter or are referred by their treating clinicians. Patients receive both written and oral information and signed informed consent, in and exclusion criteria are checked.

### Inclusion criteria

Patients age 18 – 65, diagnosed with BD (BD-I, BD-II and BD-NOS) and comorbid BPD or borderline personality features (at least 3 of 9 DSM-IV-TR criteria for BPD, including both impulsivity and anger bursts).

### Exclusion criteria

Patients with currently severe depressive (score on the Invertory of depressive Symptoms, self-rated version IDS-SR
[24] > 38) or manic symptoms (score on the Young Mania Rating Scale YMRS
[25] > 20) are excluded from the study. Other exclusion criteria are: currently having a separate treatment for substance abuse; currently receiving a separate psychotherapy; having received STEPPS within the last two years or receiving STEPPS currently; being unable to comply with the STEPPS protocol; and being unable to understand the Dutch language.

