### Objectives

#### Study part 1

Primary objective:

• To investigate the prevalence of borderline personality features in outpatients with BD.

#### Study part 2

Primary objectives:

• To investigate the effectiveness of STEPPS added to TAU on the symptoms and course of BD in patients with BD and comorbid borderline personality features.

• To investigate whether addition of STEPPS to TAU is differently associated with a decrease of frequency and severity of manic, hypomanic or depressive episodes.

• To investigate the effectiveness of STEPPS added to TAU on the symptoms, course and burden of borderline personality features.

Secondary objectives:

• To investigate whether addition of STEPPS to TAU is associated with an increase of quality of life.

• To investigate whether addition of STEPPS to TAU is associated with a decrease of utilizing mental healthcare.

• To investigate whether addition of STEPPS to TAU is associated with a decrease of psychiatric symptoms not primarily related to BD or borderline personality features.

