### Statistical analyses

Differences in baseline data between the STEPPS condition and TAU condition are analyzed by t-test for continuous variables (demographic characteristics and scores on the outcome variables). Differences in utilizing mental healthcare between both groups will also be analysed by t-test. Categorical variables will be analyzed by chi-square. Both groups will be compared to an average number of symptomatic days/year, differentiated according to severity (LCM).

Linear Mixed Model (LMM) under the missing at random (MAR) will be used to analyze questionnaires data: the severity of manic and depressive symptoms (IDS-SR & YMRS), severity and course of borderline symptoms (BPDC-47 & PAI-BOR), psychological and somatic distress (BSI total score) and quality of life (OQ-45 & WHOQol Bref).

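### Patients may enter during a mild or moderate mood episode, so the planned comparison of symptomatic days cannot by itself show an effect on recurrence

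*Protocol article*

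**What the plan says.** **Eligibility.** The protocol article, Inclusion criteria, admits "Patients age 18 – 65, diagnosed with BD (BD-I, BD-II and BD-NOS) and comorbid BPD or borderline personality features". It asks for no euthymia, remission or episode-free interval. Under Exclusion criteria, current mood state bars entry only when severe: "Patients with currently severe depressive (score on the Invertory of depressive Symptoms, self-rated version IDS-SR" above 38, or a YMRS score above 20. Under Procedure and outcome measures, the MINI-Plus verifies the bipolar diagnosis and is repeated only when the existing information is more than 2 years old, so it does not fix mood state at T0.

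**Outcome.** The Abstract states: "Primary outcomes will be the frequency and severity of manic and depressive recurrences". The Objectives for study part 2 speak of the symptoms and course of bipolar disorder, and of a "decrease of frequency and severity of manic, hypomanic or depressive episodes".

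**Analysis.** Course is recorded with the prospective LCM. Under Statistical analyses, the only LCM comparison of bipolar course is: "Both groups will be compared to an average number of symptomatic days/year", split by severity. No baseline covariate is named for it. IDS-SR and YMRS are taken at baseline, and a retrospective LCM of the past year is completed, but no use of the retrospective LCM in the analysis is stated.

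**The concern.** A recurrence, in its ordinary sense, is a new episode. A patient already in an episode at T0 cannot recur until it has ended. Symptomatic days per year, as worded, do not distinguish days of an episode already running from days of one that begins later. A lower figure under STEPPS could therefore mean that entry episodes resolved sooner, that fewer new episodes began, or both. Each is a benefit, but they are different claims, and the Abstract promises the one about recurrence.

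There is also a precision cost. Mood state at entry is likely to explain part of the variation in later symptomatic days. If the comparison ignores it, that variation stays in the error term.

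**Working it through.** **1. Do the three statements fit together?**

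| Element | Where | What it fixes |
|---|---|---|
| Population | Inclusion and Exclusion criteria | Remission not required; IDS-SR up to 38 and YMRS up to 20 admitted |
| Outcome | Abstract | Recurrences |
| Outcome | Objectives | Symptoms and course; episodes |
| LCM analysis | Statistical analyses | Symptomatic days per year by severity |

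The analysis variable fits the aim on symptoms and course. It does not isolate recurrence in a population that may start in an episode. No section defines a recurrence or says how an episode present at T0 is handled.

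**2. How many patients might be affected?** The documents give no figure for this trial. The nearest is in Background, an external network sample of 375 with bipolar I or II disorder: 169 euthymic, and "36,8% in 163 depressed patients, and 51.2% in 43 patients with current (hypo-) mania" (the percentages are those screening positive for BPD).

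- Not euthymic: (163 + 43) / 375 = 206 / 375 = 54.9%.
- Positive for BPD: 169 × 0.343 ≈ 58; 163 × 0.368 ≈ 60; 43 × 0.512 ≈ 22. The sum is 140, and 140 / 375 = 37.3%, which matches the stated overall figure.
- Not euthymic among those positive: (60 + 22) / 140 = 58.6%.

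An unknown part of these patients would exceed the trial's cut-offs, so neither figure is an expected share for the trial.

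**3. How many days could an entry episode contribute?** Assumptions, not document figures: a share p of 20% to 55% enter in an episode with d = 30 to 90 days left, and follow-up is 18 months (1.5 years). Mean contribution per patient = p × d / 1.5.

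- Low end: 0.20 × 30 / 1.5 = 4 days per year.
- High end: 0.55 × 90 / 1.5 = 33 days per year.

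This is expected equally in both arms if STEPPS does not change how fast entry episodes end.

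**4. What could the unadjusted variance cost?** The plan's own figure first: a two-sided two-sample t-test with d = 0.50, alpha 5% and power 80% needs 63.8, so 64 per group, as stated (power 80.1%).

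Now suppose that d = 0.50 holds for the outcome without entry-episode days, that STEPPS does not affect those days, and that they add variance equal to r times the remaining variance. Then d becomes 0.50 / √(1 + r). With 64 per group:

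| r | d | Power |
|---|---|---|
| 0.10 | 0.477 | 76% |
| 0.25 | 0.447 | 71% |
| 0.50 | 0.408 | 63% |

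The documents give no value for r, and Sample size does not say which outcome d = 0.50 refers to. Baseline adjustment would recover part of the loss, not necessarily all.

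**5. What if the recurrence conclusion used only patients well at T0?** With 140 × 0.90 / 2 = 63 per arm after loss, and the same assumed 20% to 55% in an episode:

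- 63 × 0.80 ≈ 50 per arm: power about 70% for d = 0.50.
- 63 × 0.45 ≈ 28 per arm: power about 45%.

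**The case against.** The strongest defence is that the Methods objectives are about symptoms, course and episodes, and that the word recurrences is in the Abstract only. For symptom burden, faster resolution of a current episode is a legitimate benefit, and total symptomatic days capture it in all randomised patients. Entry mood state is balanced between arms in expectation, and chance imbalance is already covered by the standard error of the comparison. This stands: the comparison is valid for burden, and it is not biased.

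It can also be said that a condensed article may leave LCM derivation rules and covariates to a fuller document. That stands as well. The absence of such detail is not the finding. What remains is that the article does state a population, an outcome and an analysis variable, and the last does not answer the recurrence question in the first.

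Three stronger readings are tempting and not supported:

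- A reader might infer that an episode unfinished at T0 will be counted as a recurrence. No section gives a counting rule.
- A reader might infer that a recurrence ratio will be pulled toward 1. No event count or ratio is planned.
- A reader might take 55% as the share that will enter in an episode. That sample is external and unpublished, was not screened by these cut-offs, and excludes BD-NOS, which the trial admits.

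**Conclusion.** The point holds in a limited form. Eligibility permits entry during a mild or moderate episode, the Abstract speaks of recurrences and the Objectives of episodes, and the one stated LCM comparison of bipolar course is of symptomatic days. That comparison estimates total burden without bias. By itself it does not support a statement about recurrence, because it mixes days of an entry episode with days of later ones.

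The size cannot be fixed from the documents. Under the assumptions shown, entry episodes contribute 4 to 33 days per year in each arm, and power falls to between 76% and 63% if they add 10% to 50% to the outcome variance. Both are illustrations. It would go too far to say that the trial can conclude nothing about recurrence: the prospective LCM should hold the information, provided the days are separated.

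**What to change.** Leave eligibility unchanged. Settle the following before the outcome data are examined by arm:

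1. **Adjust.** Include T0 IDS-SR, T0 YMRS and past-year symptomatic days from the retrospective LCM as covariates in the LCM comparison. All are already collected (assuming that the retrospective LCM is completed at entry; the measurement figure is not shown).
2. **Separate.** Keep total symptomatic days in all patients as the burden outcome. Beside it, report LCM days and episodes with onset after any episode running at T0 has ended, and use the term recurrence only for these. Bring the wording of Abstract, Objectives and Statistical analyses into line.
3. **Show by T0 mood state, as supportive only.** Do not rest the recurrence conclusion on patients well at T0. Under the assumed range, that would lower power to about 70% or 45%.

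The cost is one derived variable, a pre-stated rule for when an episode counts as present at T0 and as ended, and slightly more analysis. The rule needs care, because IDS-SR and YMRS measure severity and do not mark the start or end of an episode; the LCM record must supply that. No new data are needed. Days of later onset also depend on how long the entry episode lasts, so they should be read beside the total and not in place of it.

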### Objectives

#### Study part 1

Primary objective:

• To investigate the prevalence of borderline personality features in outpatients with BD.

#### Study part 2

Primary objectives:

• To investigate the effectiveness of STEPPS added to TAU on the symptoms and course of BD in patients with BD and comorbid borderline personality features.

• To investigate whether addition of STEPPS to TAU is differently associated with a decrease of frequency and severity of manic, hypomanic or depressive episodes.

• To investigate the effectiveness of STEPPS added to TAU on the symptoms, course and burden of borderline personality features.

Secondary objectives:

• To investigate whether addition of STEPPS to TAU is associated with an increase of quality of life.

• To investigate whether addition of STEPPS to TAU is associated with a decrease of utilizing mental healthcare.

• To investigate whether addition of STEPPS to TAU is associated with a decrease of psychiatric symptoms not primarily related to BD or borderline personality features.

### Procedure and outcome measures

Study part 1: The aim of study part 1 is to investigate the prevalence of borderline personality features in patients with a diagnosis of BD. After informed consent all patients with the diagnosis of BD are asked to complete the *Personality Disorder Questionnaire-4+* (PDQ-4+
[26], Dutch translation
[27]) to screen for the prevalence of BPD. After screening all patients who score positively on the presence of BPD will be asked to participate in a *Structured Clinical Interview for DSM-IV Personality Disorders* (SCID-II)
[28]; Dutch translation
[29]. The SCID-II will start with modules concerning BPD. In case of the presence of three BPD symptoms, including both impulsivity and anger bursts, the interview will be continued with modules of other personality disorders to explore further axis-II comorbidity. In case of presence of less than three BPD symptoms (including both impulsivity and anger burst) the interview will be terminated. The diagnosis of BD (inclusive subtype I, II & NOS) will be verified with modules A (depression), C (suicidality) and D (mania) of the MINI-Plus
[23]. Modules K & L will be completed to determine substance abuse, and module M part I & II will be completed to exclude schizoaffective disorder. In patients who were previously assessed with the MINI-Plus, a re-test will be completed only if the information is older than 2 years.

Study part 2: After inclusion into the trial patients are randomly assigned either to the STEPPS added to treatment as usual (TAU) for bipolar disorder or the control group receiving TAU for BD only. Patients in the intervention group will be assessed on all outcome measures at baseline (T0), at the end of the intervention (T1) and 12 (T2) and 18 (T3) months after start of treatment. Patients in the TAU control group will be assessed at baseline and at corresponding intervals. The course of BD and utilization of mental healthcare (number of consultations) is measured with the prospective version of the *Life Chart Methodology* (LCM)
[30]. At baseline all patients will be assessed with the *Borderline Personality Severity Index* (BPDSI) for severity of borderline symptoms
[31], the *Brief Symptom Inventory* (BSI)
[32] for severity of general psychological symptoms, the *Inventory of Depressive Symptomatology* (IDS-SR)
[24] for severity of depressive symptoms, and the *Young Mania Rating Scale* (YMRS)
[25] for severity of manic symptoms. The burden of borderline symptoms will be assessed with the *Borderline Personality Disorder Checklist* (BPDC-47)
[33] and *Personality Assessment Inventory – Borderline Features (PAI-BOR)*[34]*.* Quality of life will be measured with the *Outcome Questionnaire* (OQ-45)
[35] and *World Health Organization Quality of Life short version* (WHOQol Bref)
[36]. Patient empowerment will be assessed with the *Patient Activation Measure* (PAM)
[37]. To assess the illness course over the past year, all participants will complete the retrospective version of the LCM. Figure 
3 shows a summary of measures of study 2.

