### Sample size

Inclusion of 64 patients for each group has a power of 80% and an alpha of 5% to detect an average difference in Cohen’s d (0.50). Assuming a loss of 10% 140 patients will be enrolled. Patients will participate in STEPPS groups that are normally organized in the participating centers, i.e., there are no groups exclusively set up for this research population. The rationale is that in clinical practice, patients with BD and comorbid borderline personality features will be treated in routinely organized STEPPS groups, together with patients with a primary diagnosis of BPD.

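### The Design and Procedure sections give different gates to the SCID-II in study part 1; the Procedure's BPD-only gate, if followed, would understate the prevalence of borderline features

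*Protocol article*

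**What the plan says.** The only objective listed for study part 1 (Objectives) is "To investigate the prevalence of borderline personality features in outpatients with BD". The inclusion criteria for study part 2 define features as "at least 3 of 9 DSM-IV-TR criteria for BPD, including both impulsivity and anger bursts". The Background explains why the category reaches below the full diagnosis: "Patients may suffer from significant symptoms of BPD without meeting the full diagnostic criteria defined by DSM-IV-TR".

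Two sections describe the step from questionnaire to interview:

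- **Design, study part 1:** the SCID-II is given "in those patients who screened positive on BPD or borderline personality features relevant for this study".
- **Procedure and outcome measures, study part 1:** the PDQ-4+ is used "to screen for the prevalence of BPD", and then "After screening all patients who score positively on the presence of BPD will be asked to participate in a" SCID-II.

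Inside the interview, the Procedure returns to the features threshold: "In case of the presence of three BPD symptoms, including both impulsivity and anger bursts, the interview will be continued". The article gives no PDQ-4+ cut-off, describes no interviews of screen-negatives, and does not define the prevalence estimator.

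**The concern.** Taken literally, the two sections define different groups for interview, and site staff cannot follow both. The Procedure's gate is stricter than the condition being counted. A patient with three or four criteria, including impulsivity and anger, belongs to the target group, but is interviewed only if the questionnaire also classes that patient as positive for BPD.

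This affects the one objective of study part 1. Patients who were not interviewed cannot be recovered at the analysis. There is a smaller consequence for study part 2: patients below the full diagnosis, whom the protocol includes on purpose, may be identified less often through the screening route.

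**Working it through.** The plan states no figure to reproduce here. The sample size in study part 2 does not bear on this point, and no size or precision target is given for study part 1. The check is a comparison of text, followed by an identity for two-stage screening.

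**Step 1: the sections side by side**

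| Section | What is named |
|---|---|
| Objectives, part 1 | Prevalence of features |
| Design, part 1 | Gate: BPD or study-relevant features |
| Procedure, purpose of PDQ-4+ | BPD |
| Procedure, gate to SCID-II | BPD |
| Procedure, rule for continuing the SCID-II | Features threshold (three symptoms, with impulsivity and anger) |

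The Procedure names BPD alone twice before the interview, then uses the features threshold within it.

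**Step 2: direction of the bias**

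Take the SCID-II as the reference standard, and take the estimator to be SCID-II-confirmed cases divided by all screened. Both are assumptions, because the article does not define the estimator. Let

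- P = true prevalence of features;
- f = share of features cases with full BPD;
- s = probability that a full-BPD case screens positive for BPD;
- g = probability that a features case below full BPD screens positive for BPD.

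The expected estimate under the Procedure's gate is E = P × [f × s + (1 − f) × g].

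The bracket cannot exceed 1, so E cannot exceed P. It is below P whenever some features cases do not screen positive for BPD. The interview removes false positives, so they do not offset the loss.

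**Step 3: illustrative size**

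The documents give none of P, f, s or g. Assume P = 40% and s = 1, so that the only loss is among cases below full BPD. The relative shortfall is then (1 − f) × (1 − g). For example, f = 0.5 and g = 0.5 give E = 0.40 × (0.5 + 0.5 × 0.5) = 0.30.

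| f | g = 0 | g = 0.5 | g = 0.8 |
|---|---|---|---|
| 0.5 | 20% | 30% | 36% |
| 0.7 | 28% | 34% | 37.6% |
| 0.9 | 36% | 38% | 39.2% |

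The relative shortfall runs from 50% (f = 0.5, g = 0) to 2% (f = 0.9, g = 0.8). With s = 1 it is zero when g = 1, that is, when the BPD screen is loose enough to catch every features case.

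**Step 4: what remains under the wider gate**

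The Design's gate removes the loss caused by the BPD-only rule. Features cases that the PDQ-4+ misses at the features threshold are still lost, so E = P × (sensitivity of the gate). With an assumed sensitivity of 0.60 to 0.95 and P = 40%, E runs from 0.40 × 0.60 = 24% to 0.40 × 0.95 = 38%. The result is a lower bound under either rule.

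**The case against.** The strongest reply is that the Procedure's wording is shorthand for the Design's rule. The same section opens by giving the aim as prevalence of features, and its rule for continuing the interview uses the features threshold. The Background, Participants and Inclusion criteria sections all treat patients below full BPD as part of the target. The caption of Figure 1, the part 1 flow chart, abbreviates both BPD and borderline features; the figure is not shown and may settle the matter. Nothing in the article ranks the Procedure above the Design. This stands as a reason not to assert that the narrow gate will be used. It does not remove the conflict in the text, which gives no cut-off to resolve it.

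A second reply is that the bias depends on an unstated estimator. A prevalence taken from PDQ-4+ scores alone would not be affected by the interview gate, and the Background cites a figure of that kind (37.3% of 375 patients). This also stands. Confirmed cases over all screened is still the natural reading of a design that adds an interview to the questionnaire.

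A third reply is that interviewing only screen-positives is an openly described design choice, and that labelling or correction can be left to a fuller document. That is fair. Not interviewing screen-negatives is therefore no contradiction; it bears only on how the result is described.

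A reader might also infer that patients below full BPD are shut out of study part 2, or that the randomised comparison is biased. The documents support neither. Recruitment also runs through treating clinicians (Design, study part 2; Participants), and the gate operates before randomisation.

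**Conclusion.** The point holds as an inconsistency with a conditional consequence. The Design and the Procedure state different gates, and only the Design's gate fits the objective of study part 1. If the Procedure is followed as written and prevalence is SCID-II-confirmed cases over all screened, the estimate cannot exceed the true prevalence of features. It falls below it whenever a features case does not screen positive for BPD.

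The direction follows from the design under those two conditions; the size does not. The 2% to 50% range rests on assumed inputs and should not be read as an estimate for this trial. Nor do the documents support the stronger reading that the prevalence will certainly be biased, since the wider gate may be what is intended. For study part 2, the most that can be said is that some eligible patients may be missed through the screening route.

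**What to change.** Reword the Procedure to match the Design. Everyone whose PDQ-4+ meets the study's features definition (at least three borderline criteria, including both impulsivity and anger), or who screens positive for BPD, is invited to the SCID-II. The impulsivity and anger requirement should stay in the rule; a gate of any three criteria would be a third rule that matches neither section. Check that Figure 1 shows the same gate.

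Describe the part 1 result as screen-positive and SCID-II-confirmed prevalence, with all screened patients as the denominator, and say that it is a lower bound because screen-negatives are not interviewed.

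The cost is some wording and more SCID-II borderline modules than the Procedure's literal rule would need. The Design already implies those interviews, and they end early when the criteria are not met. The change is useful only if made before patients are selected for interview.
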